### Sample size

Studies on the prevention of mental disorders tend to suffer from problems of insufficient statistical power [28]. In the current study we aim to get around this problem by using a continuous primary outcome measure and by including a high risk group (selective prevention).

We decided that effect sizes of 0.35 (midpoint of small - medium effect size) or over on the total problems scale of CBCL 1.5-5 are to be detected. With alpha 5% and power (1-beta) 80%, we have to include 260 participants in our analyses. To account for some drop out we aim at 300 women entering the trial. If 50% eventually meets all criteria and gives informed consent, 600 screen-positives must be identified. The 50% rate is based on studies with psychological interventions during pregnancy aimed at reducing the occurrence of postnatal depression [27]. Given the figures in the literature [11,29] we can expect around 10% screen-positives on either the anxiety or depression screener. With an estimated 50% comorbidity between anxiety and depression this means that approximately 15% will be eligible for the randomisation. Therefore, 4000 need to be screened. Assuming a response rate of 75% [30] this implies that 5333 must be offered screening. To be on the safe side, we aim at screening 6000 women. If necessary for the recruitment of 300 women, the total number of screens may be increased.

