### Data analysis

If necessary, skewed continuous variables will be transformed to normality prior to the analyses. The primary outcome, i.e. the CBCL scores at month 18, will be compared between the treatment arms using the unpaired t-test. This test will also be used for detecting differences in the Bayley scores by month 18 and the obstetric variables measured at birth. The latter group of variables will be tested using the Chi2 test if categorical. Differences in attachment style at month 12 will be analyzed using analysis of covariance with the baseline variable as a covariate. Continuous outcomes that were measured more than twice (e.g. EPDS and STAI) will be analyzed as dependent variables using linear mixed models for fixed and random effects. These models are superior for the analysis of longitudinally correlated data and can optimally deal with missing values [53]. A mixed model ascribes a unique intercept and slope estimate to each individual, while making use of information across individuals for predicting these quantities. In these analyses, a treatment*time variable indicating the effect of the intervention will be included as an independent variable. If despite randomisation important baseline differences exist in prognostically important variables such as the extent of social support or history of life events, they will be adjusted for. Additional analyses will be conducted to demonstrate mediation of the effect of CBT on the child's outcomes by maternal symptom level, alcohol or nicotine consumption in pregnancy, medication use or neonatal outcomes.

The analyses will primarily be carried out according to the intention-to-treat (ITT) principle, i.e. the participants will be analyzed according to their randomized allocation, regardless of the actual CBT undergone, or time in study after baseline. Aside from the optimal validity of ITT analyses, they quantify the effects on the outcome measures that would be obtained in practice. The magnitude of the effect measured in an ITT analysis incorporates the effects caused by non-adherence to CBT, behavioural changes, et cetera. Secondary analyses will be of the 'per protocol' type meaning that they will be restricted to those women that had all of the CBT sessions.

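### The primary CBCL comparison is described as intention-to-treat whatever the time in study, but the planned t-test on a once-measured 18-month score is an available-case analysis by randomised arm

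*Protocol article*

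**What the plan says.** The Data analysis section names the primary test: "The primary outcome, i.e. the CBCL scores at month 18, will be compared between the treatment arms using the unpaired t-test". The same section says the analyses are primarily intention-to-treat, meaning that "the participants will be analyzed according to their randomized allocation, regardless of the actual CBT undergone, or time in study after baseline". Linear mixed models, the only method that the section links to missing values, are planned for continuous outcomes with three or more measurements, such as the EPDS and STAI.

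The CBCL is not such an outcome. Study outcome measures places it at 18 months of age, and Table 1 marks it in the last column only.

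The Sample size section states: "we have to include 260 participants in our analyses. To account for some drop out we aim at 300 women entering the trial".

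**The concern.** The stated analysis principle and the named method do not match. A t-test on a single 18-month score has nothing to work with for a woman who leaves before 18 months, so time in study does decide whether she is analysed. The repeated EPDS and STAI scores she gave before leaving play no part in the primary comparison.

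This matters because of the setting. Follow-up runs for about 24 months (Economic evaluation) in women selected for anxiety or depression. One arm is offered up to 14 therapy sessions and the other receives care as usual. The trial's premise is that maternal symptoms affect the child's outcome. If symptoms also influence who returns the CBCL, and do so differently in the two arms, the primary contrast is distorted while carrying an intention-to-treat label. The CBCL is also the effect measure of the cost-effectiveness analysis, so any distortion carries over to it.

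**Working it through.** **1. The plan's own figure.** Inputs from Sample size and Randomisation: standardised effect 0.35, alpha 5% (taken as two-sided), power 80%, 1:1 allocation.

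- Normal approximation: n per arm = 2(1.960 + 0.842)² / 0.35² = 128.2, rounded up to 129, so 258 in total.
- Exact two-sample t-test: 129.1, rounded up to 130 per arm, so 260 in total. The stated 260 reproduces.
- A one-sided alpha gives 202 and does not reproduce it.
- Loss allowed for: (300 − 260) / 300 = 40/300 = 13.3%.
- Power of the t-test is 80.3% with 260 observed scores and 85.6% with 300.

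The sample size is correct. It is the size for a t-test on women with an observed CBCL.

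**2. Which women the named method uses.**

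| Element | What the article fixes | Consequence |
|---|---|---|
| Measurement | CBCL once, at 18 months | No earlier value to carry information |
| Test | Unpaired t-test | Observed scores only |
| Missing-value method | Mixed models, for three or more measurements | Does not reach the CBCL |
| Principle | Time in study does not matter | Not delivered for the CBCL |

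**3. Size of the possible bias.** Let p1 and p0 be the proportions without a CBCL in the CBT and CAU arms. Let d1 and d0 be the mean CBCL of women without a score minus that of women with one, in SD units. In each arm the full mean equals the observed mean plus p·d. Hence

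full contrast − observed contrast = p1·d1 − p0·d0.

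A higher score means more problems, so a positive value means that the observed contrast (CBT minus CAU) flatters CBT.

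Only the 13.3% comes from the article. The gaps and the split of loss between arms are assumptions. With 150 women per arm, 15 and 25 lost (10% and 16.7%) make up the 40.

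| Scenario | Calculation | Bias (SD) | Share of 0.35 |
|---|---|---|---|
| Equal loss, equal gap | 0.133 × 0.5 − 0.133 × 0.5 | 0 | 0% |
| 10% v 16.7% loss, gap 0.3 in both arms | 0.3 × (0.167 − 0.10) | 0.020 | 6% |
| 10% v 16.7% loss, gap 0.5 in both arms | 0.5 × (0.167 − 0.10) | 0.033 | 10% |
| 13.3% loss per arm, gap 0.3 in one arm only | 0.133 × 0.3 | 0.040 | 11% |
| 13.3% loss per arm, gap 0.5 in one arm only | 0.133 × 0.5 | 0.067 | 19% |

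If overall loss were 20% rather than 13.3% (an assumption), a 0.5 SD gap in one arm only gives 0.20 × 0.5 = 0.10 SD (29%). Loss of 10% v 30% with a gap of 0.25 to 0.50 SD in both arms gives 0.20 × 0.25 to 0.20 × 0.50, or 0.05 to 0.10 SD.

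**The case against.** **Silence is not error.** A t-test can follow multiple imputation, and a condensed article may leave imputation rules to an analysis plan that is not shown. That stands: the lack of an imputation rule would be no finding by itself. What remains is that the article commits to an analysis principle and to a method that, applied as written, does not meet it.

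**The intention-to-treat sentence can be read more loosely.** Its main clause concerns analysis by allocation, and the text that follows explains it by non-adherence and contrasts it with a per-protocol analysis. On this reading, the reference to time in study only rules out excluding women for short participation. The reading is possible, but a woman with short participation and no CBCL is still left out.

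**Drop-out is not hidden.** A reader might infer that the plan conceals the loss, or that it defines the primary analysis set as 260 women. The article supports neither. It openly plans for loss ("To account for some drop out we aim at 300 women entering the trial"), and 260 is a requirement for power. Inflating the sample for drop-out is also compatible with imputation.

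**The larger figures need strong assumptions.** The 0.067 SD needs a gap in one arm and none in the other. The Background attributes at most 22% of the variance in behavioural problems to prenatal anxiety, stress or depression, a correlation of at most √0.22 = 0.47. If the gap arose only through those symptoms, and linearly, 0.5 SD in the child would need women without a CBCL to differ by 0.5/0.47 ≈ 1.07 SD on symptoms, and 0.3 SD would need about 0.64 SD. This favours the lower rows of the range. Any part of the gap that the observed data do not explain would also not be repaired by imputation, hence the need for a sensitivity analysis.

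**Conclusion.** The point holds as a mismatch between label and method. Followed as written, the primary result is an available-case comparison by randomised arm, and the intention-to-treat description does not fit it.

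At the allowed 13.3% loss, the possible bias is about 0.03 to 0.07 SD (10% to 19% of the target effect) if women without a CBCL differ by 0.5 SD, and smaller for smaller gaps. These figures rest on assumed gaps and an assumed split of loss.

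A reader might go further and infer that the primary result will be biased, or that a t-test on observed scores is valid only if scores are missing completely at random. The documents do not support this. The contrast is unbiased whenever p1·d1 = p0·d0, for example with equal loss and equal gap in both arms, and the article gives no figures on the drop-out mechanism. Nor is the comparator untreated: under Randomisation, CAU women are told of their risk and advised to see their GP, and their care is recorded. Different loss between arms is plausible but not shown.

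**What to change.** - **Primary comparison.** Include all randomised women for whom the outcome is defined. Use multiple imputation of the 18-month CBCL, by arm, from the stratification factors (parity and socio-economic position), baseline covariates, all observed EPDS and STAI scores, and birth outcomes.
- **Pregnancies without a surviving child.** State explicitly how they are handled and report their number by arm. Restricting to women with a defined outcome is itself a selection after randomisation and should be visible.
- **Sensitivity.** Add a delta-shift analysis that moves the imputed scores, including by different amounts in the two arms.
- **Supportive result.** Report the observed-case t-test, labelled as available cases by randomised arm.

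At minimum, remove the reference to time in study for the CBCL and add the imputed analysis as a pre-specified sensitivity analysis.

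The cost is wording and modest programming, since the auxiliary data are already collected. The downside is reliance on a missing-at-random model, which the delta-shift analysis probes. The planned sample size need not change.

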In the CBT arm, we expect more beneficial neonatal outcomes, in particular higher birth weight and less prematurity, which are risk factors for adverse cognitive and behavioural outcomes themselves [8]. We also anticipate reduced smoking and less drinking, with many physical and mental health benefits for the child as a result [17]. Since prenatal depression has shown to be related to postnatal depression, we hypothesize that our intervention will also counter postnatal depression, which in turn will benefit the mother - child attachment [27].

Finally, but not unimportantly, the reduction of symptoms of anxiety or depression during pregnancy and the early postnatal period is valuable in itself. It may further provide for a safer approach to reducing symptoms in pregnancy than antidepressant medication [15]

To date, no such study has been performed.

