### Setting & Design

The source population will consist of all pregnant women in the Netherlands in the first trimester of their pregnancy. Women are recruited in obstetric care. In addition, we will invite pregnant women through advertisements in regional and national media targeted at pregnant women.

Women will be screened on anxiety and depression symptoms. Women with at least moderate symptoms of anxiety and/or depression at the end of the first trimester of pregnancy are either randomized to the intervention group in which they receive 10-14 sessions of CBT, or to the control group in which they receive care as usual.

Figure 1 shows the exact design of the study.

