### Randomisation

Right after the SCID-II interview, women are randomised 1:1 to either CBT or CAU.

We will create randomisation lists, stratified for parity and socio-economic position, with randomly permuted blocks of random size.

Women randomized to the CAU arm will be informed about being at risk of depression or anxiety disorder by the researchers and will be advised to contact their GP. A close record will be kept of all care provided in the CAU arm.

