### CBT Intervention

The intervention consists of 10-14 individual sessions: 6-10 sessions during pregnancy and 4-8 sessions after delivery (once a week). The CBT will be conducted by registered psychologists, specialized in conducting CBT.

CBT posits that an individual's biased information processing leads to maladaptive feelings and behaviours which can culminate in psychological distress and eventually in psychiatric disorders. The main focus of the proposed intervention is targeted on identifying and changing dysfunctional cognitions and schemata (attitudes) specifically for pregnant depressed and anxious patients. In CBT, the Socratic dialog is used aiming to change these dysfunctional cognitions and attitudes permanently. CBT may therefore result in long term protection against psychosocial problems. It is therefore not surprising that cognitive therapy during the acute phase of depression also appears to be effective in reducing subsequent recurrence rates [25].

The first session will focus on the rationale CBT, i.e. the influence of (irrational or dysfunctional) cognitions and attitudes on feelings and behaviours. Additionally, goal setting will be initiated. These therapy goals will be unique for each patient. The subsequent sessions will be targeted at identifying and amending irrational cognitions and attitudes related to pregnancy, delivery, concerns about the (unborn) child and the future family situation. Each session will address specific pregnancy-related cognitions. Additionally, patients will be taught how dysfunctional cognitions and attitudes affect adversely feelings and behaviours.

These dysfunctional cognitions and attitudes will be challenged and replaced by functional cognitions and attitudes. After each session, patients will be given home work. For example, patients will be asked to register negative experiences, and accompanying cognitions, feelings and behaviours. Finally, in the last two to four sessions, the newly learned cognitions and attitudes will be consolidated.

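### The secondary per-protocol analysis selects only the CBT arm, on attendance after randomisation, so it is open to selection bias of unknown direction

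*Protocol article*

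**What the plan says.** The Data analysis section of the protocol article sets the order of the analyses: "The analyses will primarily be carried out according to the intention-to-treat (ITT) principle". For the primary outcome, the CBCL total problems score at 18 months, the arms "will be compared between the treatment arms using the unpaired t-test". It then adds: "Secondary analyses will be of the 'per protocol' type", and defines this by saying that "they will be restricted to those women that had all of the CBT sessions". The only covariate adjustment described for between-arm comparisons of this kind is for baseline imbalance; none is described for selection into completion.

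The CBT Intervention section gives the course: "The intervention consists of 10-14 individual sessions: 6-10 sessions during pregnancy and 4-8 sessions after delivery (once a week".

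The Setting & Design section allocates the other women "to the control group in which they receive care as usual". The Randomisation section says "A close record will be kept of all care provided in the CAU arm", but no per-protocol criterion for that arm is built on this record.

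**The concern.** A per-protocol result is usually read as the effect of receiving the full treatment. Here the rule that decides membership is attendance at CBT sessions, which happens after randomisation and exists in one arm only. On the natural reading, women who finished CBT are compared with all CAU women. Finishers may differ from non-finishers in ways that also bear on the child's score, while the CAU arm still contains both kinds of women. The difference then mixes any effect of CBT with the difference between women who finish and women who do not.

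The word 'all' is also loose. With a course of 10 to 14 sessions it could mean any of five totals, or whatever number was planned for the individual woman. Two women with 10 sessions each could be classed differently, and the choice could be made after outcomes are known.

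At stake is a secondary claim about full CBT that could appear when CBT does nothing, or vanish when it works.

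**Working it through.** **Design figure first.** Inputs from the Sample size section: effect 0.35 SD, alpha 5%, power 80%, 260 analysed, 300 entering. The two-sided normal formula gives 129 per arm, 258 in total. The t-test solution is 129.1, rounded up to 130 per arm, or 260, with power 0.803. The plan's figure reproduces, so 0.35 SD is used as the yardstick and 130 per arm as the analysed size.

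**Shift under no effect.** Let c be the share of CBT women who complete, and gap the difference in mean outcome (in SD, positive = better) between those who would complete and those who would not. With no CBT effect, the CAU mean equals the whole CBT-arm mean, so

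shift = completer mean − CAU mean = (1 − c) × gap.

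To vary c and the strength of selection together, take the tendency to complete and the outcome as bivariate normal with correlation rho. Then

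shift = rho × φ(z) / c, with z the (1 − c) normal quantile.

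The document gives neither c nor rho; both are assumptions. The multipliers φ(z)/c are 0.280/0.8 = 0.350, 0.386/0.6 = 0.644 and 0.386/0.4 = 0.966.

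| Completion c | rho = 0 | rho = ±0.1 | rho = ±0.2 | rho = ±0.3 |
|---|---|---|---|---|
| 80% | 0 | ±0.035 | ±0.070 | ±0.105 |
| 60% | 0 | ±0.064 | ±0.129 | ±0.193 |
| 40% | 0 | ±0.097 | ±0.193 | ±0.290 |

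Positive values favour CBT. The extreme, 0.290/0.35, is 83% of the target effect. In terms of the gap, rho = 0.3 means 0.105/0.2 = 0.53, 0.193/0.4 = 0.48 and 0.290/0.6 = 0.48 SD between completers and non-completers. With rho = 0 there is no bias.

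**Effect on the test.** Completers number 130c, and the standard error is √(1/(130c) + 1/130). At c = 60% this is √(1/78 + 1/130) = 0.143. With rho = ±0.2 the shift is 0.129/0.143 = 0.90 standard errors, and the two-sided false-positive rate is 15% instead of 5%. At 80% and 40% completion it is 8% and 22%.

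**Check on the remedy.** Suppose an instrumental-variable estimate defines exposure as reaching a threshold. With share c above it (effect d) and share q having partial courses (effect e), the estimate is (c·d + q·e)/c = d + (q/c)·e. It is too large by (q/c)·e unless partial courses do nothing. With c = 0.6, q = 0.4 and e = d/2 (assumptions), the excess is (0.4/0.6) × 0.5 = 0.33 of d. Using the session count as exposure avoids the threshold but assumes that each session adds the same amount.

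**The case against.** The strongest defence is that nothing primary depends on this. Intention-to-treat comes first, the protocol explains why, and the per-protocol analysis is explicitly secondary. That stands, and it limits the weight of the point.

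It is also fair that a condensed article may leave the session threshold and the CAU criterion to the full protocol or analysis plan. Neither gap is a finding in itself. But the article does state the restriction, and any threshold applied to CBT attendance alone would still select one arm.

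Three stronger readings are tempting, and the document does not support them.

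- *The analysis has no control group.* Taken word for word, no CAU woman can meet the rule. But the section is about comparing arms, and the sentence is most naturally the adherence criterion for the CBT arm.
- *The bias favours CBT.* Completers may be more motivated or stable. Equally, women who improve early may stop, and women with persisting symptoms may finish. The document does not say which. A range built only on positive gaps would fix the sign by its inputs.
- *Preterm births are filtered out of the CBT arm.* The Background says "In the CBT arm, we expect more beneficial neonatal outcomes, in particular higher birth weight and less prematurity" and treats these as risk factors for the child's outcome, but it does not link them to completing CBT. Six antenatal sessions can suffice. If they are weekly (the stated frequency may cover only the postnatal ones) and start at an assumed week 14-20, the sixth falls at week 19-25, before most preterm births. A complicated birth could still disrupt postnatal sessions, but that is one possible route, not a documented one.

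**Conclusion.** The point holds for the secondary per-protocol analysis only. Followed as stated, the rule gives a contrast selected in one arm on post-randomisation attendance, with no adjustment for that selection and no single meaning for completion. The result is open to bias of unknown direction. Its possible size, -0.29 to +0.29 SD against a target of 0.35 SD, rests on assumed completion of 40-80% and an assumed correlation of -0.3 to +0.3 under a bivariate normal model; it is a sensitivity range, not an estimate. The sample size, the primary t-test and the intention-to-treat result are untouched. This is a worthwhile and cheap improvement, not a threat to the trial's main conclusion.

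**What to change.** Replace the completer restriction with a complier-average estimate by instrumental variables (two-stage least squares), with randomised arm as the instrument. Include all women with an 18-month outcome, in both arms as randomised; by the plan's own figures that is about 260 of the 300 entering. Use the number of CBT sessions attended as the main exposure, with the linear dose effect stated as an assumption. Add a version with a prespecified minimum course as a sensitivity analysis, and note that it overstates the effect if partial courses help.

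If a per-protocol result is still reported, fix the meaning of completion before outcomes are seen, name CAU as the comparator and label the result exploratory.

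The cost is a change of analysis wording. The interval will be wider than that of the per-protocol contrast. The exclusion restriction (allocation affects the child's score only through the sessions attended) and linearity must be stated. The article does not list CBT attendance among its data, so its recording should be confirmed, but the existing rule cannot be applied without it.
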